### Statistical analysis

#### Population of statistical analysis

##### Full analytical set (FAS)

This term refers to the set including finished and shedding cases but excluding rejection cases. This group includes those who has taken at least one medication and were recorded in at least one follow-up.

##### Per-protocol set (PPS)

This term refers to cases that meet the inclusion criteria, did not meet the exclusion criteria and completed the treatment plan. In other words, the cases that meet the trial plan, have good compliance and complete the contents prescribed by the CRF will be analysed. PPS will be used to analyse the main indicators for evaluating efficacy and to assess for conformance with FAS results.

### Statistical analysis methods

The data of this clinical trial will be analysed using SPSS Statistics 26.0 statistical software. First, the baseline situation of the two groups of patients will be analysed to ensure that the baseline of the treatment group and the control group are balanced. Normal tests will be performed for measurement data. Continuous variables conforming to a normal distribution will be represented by the mean and standard deviation. Two-independent sample *t*-tests will be used for two groups that conform to a normal distribution, and paired sample *t*-tests will be used for comparison of the same sample before and after comparison. Counting data will be represented by percentages, and the chi-square test will be adopted. For continuous variables that do not conform to the normal distribution, the median will be used, and the independent sample Wilcoxon rank sum test will be used for the two groups. The paired sample Wilcoxon rank sum test will be used for the comparison of the same sample before and after. The Wilcoxon rank sum test will also be used for ranked data. *P* ≤ 0.05 will be considered statistically significant.

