**Fig. 1 Fig1:**
[figure not shown]
The study flow chart of the whole multicentre RCT

We will record all baseline observations involved during the screening period. During the period of treatment, all participants will be required to record BMI and waist values daily. Routine blood tests, routine urine tests, routine stool tests, and blood biochemistry will be performed and recorded every 3 months. Intraperitoneal fat thickness (imaging MRI measurement of fat layer thickness) will be measured and recorded once each before and after treatment. After the end of the last treatment, all patients will enter the posttreatment follow-up period. All subjects will be followed up once a month. The schedule of participants is shown in Fig. 2.

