The study aims to recruit 266 participants (4 units in total). The four units include the following major leading and undertaking units. The Longhua Hospital affiliated with Shanghai University of traditional Chinese Medicine, which will recruit 86 participants. The remaining participating units will recruit 60 participants each: Yueyang Hospital of Integrated Chinese and Western Medicine affiliated with Shanghai University of traditional Chinese Medicine; Shanghai Jinshan Hospital of Integrated Chinese and Western Medicine; Shanghai Pudong New District People’s Hospital. Each unit is responsible for the specific responsibilities of the study, including recruiting patients and collecting specimens and data. Laboratory testing and imaging examination will be performed in the corresponding departments of each unit. Data analysis will be performed at the Clinical Research Center of Longhua Hospital affiliated with Shanghai University of Traditional Chinese Medicine.

To ensure the safety of the participants, blinding, data quality, and adherence to the study protocol, personnel directly participating in this study will be completely trained and will follow Good Clinical Practice (GCP) guidelines.

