#### Sequence generation

The method of central stratification and block randomization will be adopted. SAS software will be used to make a random sequence table to generate random numbers as drug numbers.

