## Evaluation

### Primary outcome

Effective rate of a 1% decrease in HbA1c and 3% decrease in body weight.

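### The between-arm tests are fixed as unadjusted although randomisation is stratified and baseline values are recorded: valid but inefficient, and the within-arm tests cannot show an effect of DDG

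*Protocol article*

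**What the plan says.** All references are to the protocol article.

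- **Design.** Sequence generation: "The method of central stratification and block randomization will be adopted". Subject screening and selection sets a total of 266 over four hospitals, one with 86 participants and three with 60 each, and leaves laboratory and imaging work to each hospital's own departments.
- **Baseline data.** Study design, in the text below Fig. 1: "We will record all baseline observations involved during the screening period".
- **Primary outcome.** "Effective rate of a 1% decrease in HbA1c and 3% decrease in body weight", a yes/no response defined by change from baseline.
- **Between-arm tests.** Statistical analysis methods: "Counting data will be represented by percentages, and the chi-square test will be adopted"; "Two-independent sample *t*-tests will be used for two groups that conform to a normal distribution"; and the Wilcoxon rank sum test where normality fails.
- **Within-arm tests.** Paired t-tests "will be used for comparison of the same sample before and after comparison", or the paired Wilcoxon test.
- **Between-arm use of baseline.** Baseline is analysed "to ensure that the baseline of the treatment group and the control group are balanced".

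The article names no centre term, stratified test, ANCOVA or regression model.

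**The concern.** Two separate matters arise in the same section.

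**Efficiency.** Stratified blocks balance the arms on the stratification factor. If that factor predicts outcome, an analysis that ignores it counts between-stratum variation as noise, and the standard error comes out too large. Local laboratories make some centre difference plausible. Baseline matters in the same way. Response requires a fall of 1% in HbA1c, and eligibility caps HbA1c at 9% but sets no floor, so starting level may well bear on who responds. A balance check does not recover this information, and the article does not say what follows if imbalance is found.

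**Interpretation.** Participants have taken no anti-diabetic drug before entry. Both arms then start metformin and follow the same diet and exercise regimen, so improvement is expected in both. A significant before-after test in the DDG arm would not separate DDG from that shared treatment.

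At stake is power that could be had at no cost, in a trial with little to spare on its own stated inputs, and a set of P values that could be misread.

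**Working it through.** **Inputs from the article.** Means 0.85 and 0.5, so a difference of 0.35; SD 1.4; alpha 0.05; beta 0.2; 1:1 allocation; 10% loss; 266 in total (Sample size calculation). The formula prints a one-sided Z, but sidedness is not stated in words, and its margin term is given no value. Both one- and two-sided results are shown, with that term set to zero.

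**1. The plan's own figure.** n per arm = (Z_alpha + Z_beta)² × 1.4² × 2 / 0.35² = (Z_alpha + Z_beta)² × 32.

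- One-sided: (1.645 + 0.842)² × 32 gives 198 per arm, or 220 after 10% loss (440 in all).
- Two-sided: (1.960 + 0.842)² × 32 gives 252 per arm, or 280 after loss (560 in all).

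The 133 per arm is not reproduced. That is a separate problem. It matters here only because it leaves little power to give away.

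**2. Continuous outcomes, unadjusted.** Evaluable per arm: 133 × 0.9 = 119.7, taken as 120. SE = 1.4 × √(2/120) = 0.1807, and 0.35 / 0.1807 = 1.936. Two-sided power = Φ(1.936 − 1.960) = 49%; one-sided = Φ(1.936 − 1.645) = 61%.

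**3. Continuous outcomes, adjusted for baseline.** Read 1.4 as the SD of change and let ρ be the correlation of baseline with the change. SE becomes 0.1807 × √(1 − ρ²). The article gives no ρ; 0.3 to 0.5 is assumed.

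- ρ = 0.3: SE 0.1724, variance down 9%, power 53% two-sided, 65% one-sided.
- ρ = 0.5: SE 0.1565, variance down 25%, power 61% two-sided, 72% one-sided.

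With no loss (133 per arm, SE 0.1717), two-sided power goes from 53% to 57% and 65%.

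**4. Binary primary outcome.** The article gives no responder rates, so this is a simulation on assumed values: 240 evaluable in centres of 78/54/54/54, control response about 30%, treatment log odds ratio 0.75, one standardised baseline covariate, and 3,000 runs per scenario. Two-sided power (%):

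| Centre SD (logit) | Baseline coefficient | Chi-square | Mantel-Haenszel by centre | Logistic, centre + baseline |
|---|---|---|---|---|
| 0 | 0.5 | 76.6 | 76.2 | 79.0 |
| 0 | 1.0 | 66.6 | 66.3 | 73.4 |
| 0.3 | 0.5 | 75.1 | 75.3 | 77.2 |
| 0.3 | 1.0 | 66.5 | 66.6 | 73.9 |
| 0.6 | 0.5 | 73.9 | 74.7 | 76.9 |
| 0.6 | 1.0 | 63.9 | 64.6 | 72.7 |
| 1.0 | 0.5 | 65.4 | 70.8 | 72.3 |
| 1.0 | 1.0 | 55.2 | 59.3 | 67.1 |

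Up to a centre SD of 0.6, stratifying by centre alone gains at most about 1 point. Adding baseline gains about 2 to 3 points at coefficient 0.5 and 7 to 9 at 1.0. With no baseline effect, the adjusted model gains between −0.1 and 1.4 points over the same range of centre SD. Only at a centre SD of 1.0 does centre itself matter (4 to 6 points). There the chi-square test's type I error falls to between 2.5% and 3.6%, which is the conservatism described above. Elsewhere its type I error lay between 4.1% and 5.5%.

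**5. Within-arm tests.** No arithmetic applies. They are separate calculations and take nothing from the between-arm comparison. Their limit is that each contrasts DDG plus metformin, diet and exercise with the state before treatment, not with placebo plus the same background.

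**The case against.** **The tests are valid.** Under randomisation, an unadjusted t or chi-square test already allows for chance baseline imbalance in its standard error, and ignoring strata errs towards conservatism. This stands. A reader might infer bias or a raised false-positive rate; neither follows.

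**This is a condensed article.** Covariates and centre handling are often left to the full protocol or the SAP. That would answer a complaint of silence. Here the article names the tests for every type of outcome, so the point concerns a stated choice. Nothing in the article rules out adding an adjusted analysis, which makes the repair easy.

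**Stratification by centre is inferred.** The factor is never named, and the article also uses the word centre for the body that distributes the drug, so the phrase could describe central administration. With four recruiting hospitals, stratification by hospital is the more natural reading, but it remains a reading.

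**The gain for the primary outcome is small or unknown.** This stands too. The 49% to 61% range is for a comparison of means and must not be carried over to the responder rate. The entry limits on HbA1c and fasting glucose may also narrow the baseline range and weaken its prognostic value.

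**Other stronger readings that the text does not support:**

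- That baseline data serve only the balance check. They also define the change-based primary outcome and enter the paired tests; only their use as covariates is absent.
- That the paired tests waste power. They do not.
- That baseline significance tests are prescribed. The article says baseline will be analysed and names no test for that purpose.
- That within-arm P values are meant as the efficacy evidence. The design is a parallel placebo comparison, and before-after description also serves the stated interest in rebound after treatment stops.

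**Conclusion.** The point holds as a recommendation on efficiency, plus a caution on interpretation. The stated between-arm analyses omit the stratification factor and the recorded baselines. They are valid, less powerful than they could be, and conservative if the stratification factor is strongly prognostic.

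For continuous outcomes the gain is about 4 to 12 points of two-sided power at 120 per arm. This rests on 1.4 being the SD of change and on an assumed correlation of 0.3 to 0.5. For the primary outcome only the direction is established: its size depends on responder rates, centre differences and baseline strength that the article does not give.

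The within-arm tests do no harm to the main comparison but carry no evidence about DDG itself. This should be changed; it does not invalidate the trial.

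**What to change.** - **Primary outcome:** logistic regression with treatment, centre (or whatever stratification factor was actually used), baseline HbA1c and baseline weight. A stratified or standardised risk difference is an alternative and stays on the scale of the effective rate. Report the effect with its 95% CI.
- **Continuous outcomes:** ANCOVA with baseline value and centre, reporting the between-arm difference and 95% CI.
- **Stratification:** name the factor or factors used in the randomisation.
- **Within-arm comparisons:** label them descriptive only, with no efficacy conclusion drawn from them.

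The cost is wording in the analysis section or SAP, settled before unblinding. The covariates are already recorded, so no new data or visits are needed.

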## End of trial

The trial will end once 266 participants have been recruited and all have completed 24 weeks of treatment and 24 weeks of follow-up.

## Ethics and dissemination

### Ethical approval and supervision

Prior to entering the study, written informed consent will be obtained from all participants. Voluntary participation will be ensured, and maximum confidentiality of information provided during the interview will be required. The trial will be supervised by the Ethics Committee. Any moderate or serious adverse events will be reported to the Ethics Committee. Participants with adverse reactions during the trial will receive free medical care.

### Confidentiality

All research-related information will be securely stored at the research site. All participant information will be stored in a locked file cabinet in a restricted access area. All laboratory samples, reports, data collection, processes and management forms will be identified by coded ID (identification) numbers only to maintain the confidentiality of participants. All records containing names or other personal identifiers (such as informed consent) will be stored separately from research records identified by code numbers. All local databases will be protected using password-protected access systems. Tables, lists, logs, dating books and any other list linking participant ID numbers to other identification information will be stored in separate locked files in the access-restricted area.

### Patience and public participation

The relevance and necessity of research questions, research design and patient-oriented documents (including informed consent, participant information tables, symptom diaries, all follow-up forms and promotional materials) have been reviewed by the public. The public engagement group consists of experienced and inexperienced people. We will try to work with the patient advocacy group to ensure that easy-to-understand language abstracts of research results are shared with participants and a wider group of patients. The burden of intervention will be assessed in a comprehensive and reasonable manner through communication between participants and researchers.

The results are not directly communicated to the participants, but the final results will be released. During the follow-up period, each participant will be informed of all examination results.

## Discussion

At present, China has become the country with the largest number of diabetic patients, and T2DM with obesity in China accounts for approximately 60% of all diabetic individuals. The pathogenesis of T2DM is a progressive disorder of islet cells with gradually diminishing effects and decreasing insulin secretion, leading to an increase in plasma glucose [22]. According to relevant studies, obesity can lead to insulin resistance, thus exacerbating the process of T2DM, which is extremely unfavourable to the recovery of patients. For T2DM patients with obesity, obesity should be treated first if T2DM is to be effectively controlled. However, currently, few effective clinical treatment options are available. The usage of sulfonylurea, nateglinide, thiazolidinedione and insulin will increase the weight of patients. Dipeptidyl peptidase-4 inhibitors and α-glucosidase inhibitors are not ideal for weight loss, and sodium-dependent glucose transporter 2 inhibitors are associated with ketoacidosis, urethral mould infection and other risks as well as high medical expenditures [23]. Therefore, in this study, metformin was selected as an intervention drug in patients with good islet function and no contraindication to metformin [24].

However, there are many metabolic disorders in patients with T2DM and obesity. These disorders lead to more complex treatment, requiring increased drug doses or combinations of multiple drugs, resulting in increased adverse reactions and reduced treatment compliance [12]. One of most common disorders is dyslipidaemia. Although statins are the most commonly used lipid-lowering drugs in the clinic, with increased medical research and the expansion of the patient population in recent years, it has been found that long-term use of statins can increase the risk of new diabetes [25] and may affect plasma glucose control in diabetic patients [26].

In clinical practice, doctors need to consider both short-term efficacy and long-term prognosis and comprehensively consider the medical burden. Traditional Chinese medicine (TCM) exhibits the characteristics of safety and reliability in long-term applications and offers multitarget and multipathway control of disease progression. DDG has been prescribed by Longhua Hospital and explored as a famous old Chinese medicine. After approximately 10 years of clinical application, DDG has obtained good clinical curative effects. After treatment, the quality of life of the patient improved. In addition to lowering plasma glucose, the patients lost weight, reduced blood lipids, improved the metabolic disorders of glucose and lipids, and reduced the risk of cardiovascular and cerebrovascular diseases. No serious adverse reactions were observed.

However, there is a lack of large-sample studies for the clinical validation of DDG, and our previous study is a single-centre self-control study, which has some limitations. Therefore, we hope to further objectively evaluate the clinical effectiveness of DDG through a multicentre, double-blind, randomized, controlled study and comprehensively evaluate the benefits of the intervention in patients with T2DM complicated with obesity from the aspects of blood lipids, plasma glucose, insulin resistance and a chronic inflammatory status. In addition, safety indexes, such as routine blood tests, routine urine tests, routine faecal tests, liver and kidney function tests and electrocardiograms, will be monitored before, during and after treatment to evaluate the safety of DDG. Finally, the follow-up period of this study is 24 weeks. Such a long follow-up period is useful to further explore whether weight rebound and index recovery would occur after stopping intervention. This follow-up is useful to objectively and comprehensively evaluate the clinical efficacy and safety of DDGs to provide a new drug choice for clinical treatment that can effectively improve T2DM with obesity.

However, the study design still has some limitations. First, the placebo contains only excipients, such as sucrose, lactose and dextrin, which may have an impact on indicators in T2DM patients with obesity. In addition, DDG is a TCM granule with special odours. Theoretically, the placebo should be consistent with DDG in colour, shape and odour, but it may be difficult to achieve complete consistency in practice. Second, our experiment will be conducted in four centres in the same region of China, and it is uncertain whether similar results will be obtained in other regions and races.

### Trial status

Recruitment will start in 01 June 2021. The current protocol version is 2.0, dated 07 September 2020.

## Data Availability

Not applicable.
